**Aim 2: Test whether gamification influences participant retention and compliance**

Hypothesis: There will be a significant difference in retention and compliance between gamified and non-gamified electronic administration of surveys. Gamification will improve retention and compliance, such that administration on the gamified app will have higher retention and compliance compared to administration on the non-gamified websites (Datacubed Health website and third-party website).

**Aim 3: Test whether the format of survey administration influences the self-reported usability of the survey format**

Hypothesis: There will be a main effect of the format of survey administration on self-reported usability of the survey format. Usability will be derived from a self-report usability survey that assesses the ease of use and pleasantness of the survey format; an overall measure of usability as well as different factors of usability will be derived from the survey responses.

Administration on paper will result in the lowest usability, and electronic administration on the gamified mobile app will result in the highest usability. Electronic administration on the non-gamified websites will result in intermediate usability, with use of Datacubed Health's website resulting in usability equivalent to or superior to a third-party website (i.e., paper < third-party website < Datacubed Health website < mobile app).

**Aim 4: Test whether payment schedule influences retention and compliance differently by format of instrument administration.**

Hypothesis: There will be a significant difference in retention and compliance between participants who receive biweekly payments and participants who receive one payment, adding up to the same amount, at study end. All participants will receive \$5.00 for each completed survey. Participants who receive payment at study end will show reduced retention and compliance, and this will vary by format of survey administration (mobile vs. Datacubed web vs. third-party web vs. paper).

**Aim 5: Test whether gamification of cognitive tasks influences participant experience and technology acceptance.**

Hypothesis: Compared to participants who complete standard, non-gamified cognitive tasks (e.g., NIH Toolbox), participants who complete equivalent, gamified cognitive tasks within Datacubed Health's app will report a more positive experience on a usability/Technology Acceptance Model (TAM) questionnaire. Delivering cognitive tasks in a gamified format on mobile device will increase standard TAM outcomes (e.g., perceived ease of use, perceived usefulness, attitude towards using, behavioral intention to use).

**Exploratory Aim 1: Test whether participant churn can be predicted from objective measures of participant engagement with the gamified smartphone app**

Hypothesis: Participant churn (i.e. dropout) will be predicted by measures of participant engagement with the gamified smartphone app. This analysis will be restricted to Arm A participants assigned to the gamified smartphone app condition. Churn will be defined as missing more than 25% of assigned instruments within a study phase (the 1 month, 3 month, and 6 month milestones). Potential markers of engagement will included the number of clicks on the avatar, number of changes made to the avatar, number of gem store purchases, and the total amount of time spent on the app.

**Exploratory Aim 2: Develop novel markers of participant behavior based on objective information from app use**

Hypothesis: Geolocation data can be used to quantify and characterize the daily routines of participants, identifying markers consistent with self-reported activities and deviations from routine. Geolocation will be used to identify and classify spatiotemporal areas of interest and develop a data-driven model of daily routine. An activity tracker will be used to capture a self-report measure of daily activities. This analysis will be restricted to Arm A participants assigned to the gamified smartphone app condition.

### 3) BACKGROUND

The widespread availability and adoption of smartphones by people across all demographics and throughout the world has opened new and exciting frontiers of research that would have been unthinkable even ten years ago. The recent ubiquity of powerful computers with sophisticated graphics capabilities and built-in sensors that people carry with them all the time is beginning to transform research on health, behavior, and cognition. More and more research and clinical trials are going 'siteless,' opting to administer assessments remotely on mobile devices rather than in-person.

Missing data due to poor participant retention (i.e. dropout from the study and/or loss to follow-up) and compliance (i.e. missing or incomplete measurements) can jeopardize the scientific validity of studies and drive up the cost of conducting research and clinical trials. The National Academy of Sciences found patient dropout rates to be as high as 30% in clinical trials, prompting calls for better trial design and conduct to limit the impact of missing data. Missing data can threaten the scientific validity of findings by introducing unintended bias and reducing statistical power, increasing the possibility that studies will fail to find effects where they exist (i.e. Type II errors). Siteless clinical trials may face additional challenges, since remote studies leave participants to their own devices and may eliminate direct contact with members of the research team. Fortunately, technology and behavioral science offer an opportunity to address these challenges in novel ways by enabling more patient-centric practices to be implemented, which may ultimately accelerate research and drug development.

One promising non-financial, tech-enabled strategy for user engagement and retention that has emerged outside of clinical research is gamification: the application of game-like features such as points, avatars, and progress-trackers in a non-game context. Offering gamified platforms for research has received considerable attention as a potential alternative way to encourage participants to complete study activities that could augment or potentially even replace financial incentives. Gamification is hypothesized to be effective at engaging individuals by serving as an intrinsic motivational affordance, such that individuals are motivated by game elements because they satisfy intrinsic psychological needs for autonomy, relatedness, and competence. While gamification of the user experience within smartphone apps for the collection of research data is both intuitively and theoretically appealing as a tool for incentivizing participation, no published study to our knowledge has directly tested whether gamification of a smartphone data collection system improves longitudinal participant retention and engagement. This study will address this knowledge gap.

An exploratory aim of the study is to develop novel objective measures of participant behavior based on data from phone sensors (specifically the geolocation, step-counter, and screen on/off times from the phone). Data-driven measures of behavior have great potential to enable better, more objective and sensitive assessments of health-related behaviors. For example, new objective measures of the amount individuals exercise (based on location and step counter data) or sleep (based on location and screen on/off data) would be useful for assessing changes in the health-related behavior of individuals following interventions as diverse as motivational interviewing, sleep medications, and dementia. Once established and validated,

sensor-based measures can be deployed directly onto individuals' phones, eliminating the need to collect or store raw geolocation data or other sensitive sensor-based information. (Please refer to attached whitepaper on location-based services for additional information.)

More sophisticated novel indices of behavior based on information such as phone location, step-counter output, and screen on/off data also have immense potential for health-related research and possible prediction of health outcomes. For instance, quantitative indices that characterize the regularity of people's daily routines, which can identify when an individual's activity begins to deviate abnormally from their own norm (e.g. when the individual begins spending much more or much less time at home than usual, or suddenly sleeps and wakes at irregular hours), could be useful both for measuring changes in behavior, and for predicting health outcomes. For example, among people with bipolar disorder, sudden changes in an individual's routine might presage an episode of mania or depression. Detection of subtle early warning signs of an approaching behavioral episode or the onset of a disease using phone-based behavioral metrics would open the door to early interventions.

To test whether electronic and gamified tools delivered on smartphones can improve retention, compliance, and participant engagement, this study will directly compare retention and compliance between groups of participants assigned surveys administered in different formats: paper, two non-gamified web platforms, and a gamified mobile app. Additionally, we will evaluate the impact of gamification of standard, widely-used cognitive tasks (e.g., Stroop Task, Wisconsin Card Sort Task) on technology acceptance (e.g., perceived ease of use, perceived usefulness, attitude towards using, behavioral intention to use, etc). The study will also examine an exploratory aspect of the study, prediction of participant dropout (i.e. churn), at different phases of the study using objective markers of engagement with the gamified mobile app. We plan to further leverage the unique capabilities of mobile devices in the gamified mobile app group to gather phone-based behavioral data (i.e. geolocation, step-counter, screen on/off times, and battery life) and develop novel behavioral metrics (e.g. quantitative measures of daily routine regularity), which we will validate relative to the self-reported information from surveys. Smartphone-based data collection opens unique opportunities to address retention and compliance, identified as major problems for clinical trials, and enables collection of denser longitudinal data and derivation of novel measures from sensor data.

#### **4) INCLUSION AND EXCLUSION CRITERIA**

Participants must be 18-89 years of age, reside in the United States, have access to Google Chrome or Safari internet browser (on a computer, tablet, or phone) and email, and be able and willing to complete and return one to two surveys per week. Participants must also own an Android or iOS smartphone (manufactured in 2014 or later) with an operating system capable of supporting the study app (Android 6.0 or greater; iOS 10.0 or greater) and with an active data plan (1GB/month or more). Potential participants will be asked to indicate that they understand English well enough to comprehend the informed consent documents and study instructions. English language abilities will be confirmed using comprehension questions during the consent process (see Section 29). No individuals unable to demonstrate they are capable of giving informed consent in English by correctly answering these questions will be enrolled. During consent, we will ask participants if they have any prior experience with the study smartphone app. Participants who indicate prior experience with the study smartphone app will be excluded from the study and will be considered ineligible.

We will not collect information about pregnancy or exclude subjects based on pregnancy status because the study will only involve use of a smartphone app and no other interventions or procedures. We will not recruit prisoners. We will not recruit minors under the age of 18.

#### **5) STUDY-WIDE NUMBER OF SUBJECTS**

We plan to enroll up to 400 individuals in the study (see Section 9).

#### **6) STUDY-WIDE RECRUITMENT METHODS**

Potential participants are expected to be recruited over the course of one year, starting at the end of Q3 2020 or start of Q4 2020. An advertisement in the Metro newspaper will be placed to recruit potential participants; both a print ad (in the physical print Metro newspaper in New York City) and an electronic ad (on Metro's website) will be placed. Electronic ads will be placed in

the New York City page of the Craigslist website, specifically in the ‘Volunteers’ section. Electronic ads will be posted on Facebook and Instagram, and links will be posted on Facebook and Reddit groups that include primarily adult participants located in the United States. The study will also be posted to online participant recruitment platforms including, but not limited to, User Interviews and Autocruitment. The print Metro newspaper is free and accessible from distribution racks placed inside 100 New York City subway stations; the websites and social media platforms are free and accessible to anyone with an internet connection.

The source of participants will be people who self-report living in the United States who meet one of the following criteria;

- Read the physical print Metro newspaper or the Metro website
- Use Craigslist, Instagram, Facebook, or Reddit.
- Are part of third-party websites (e.g., User Interviews, Autocruitment) which function to connect participants with user research studies.

A copy of the ad (print and online) is included as an attachment in this application. The ads include the following information:

- Description of Datacubed Health
- Description of the study design + objectives
- Eligibility requirements for study participation
- Study participation requirements: completion of approximately one survey per week
- Compensation for study participation: \$5 for each survey or task completed
- Contact information for Datacubed Health (link to website)

Potential participants who are interested in the study will visit the website listed on the study ad. This website will be hosted on Datacubed Health’s secure servers and will contain additional information about the study. The complete study website text is included as an attachment. Those who review the information on the website and wish to participate will be directed to an online screening questionnaire. The study team will then invite those potential participants whose screening questionnaires indicate that they meet study inclusion criteria to review and sign the study consent form online through Datacubed Health’s web-based platform (see Section 29 for further details on consent process).

Datacubed Health will inform potential participants whose screening questionnaires indicate that they do not meet study inclusion criteria that they have not been selected to participate in the study.

## **7) STUDY TIMELINES**

Each participant will be asked to complete surveys for six months after enrollment. Over the course of that six-month period, they will receive roughly one survey each week either by mail, within the smartphone app, through the Datacubed Health website, or through a third-party

website. Each survey will last no longer than 10 minutes, but most will be shorter (~3 minutes). A subset of participants who complete the initial six-month period will be given the option to continue into a two-week follow-up period, during which they will complete up to 6 more activities (cognitive tasks and usability/TAM surveys).

We plan to enroll all participants in the study within one year. We plan to complete primary analyses of the study data within two years.

## 8) STUDY ENDPOINTS

The primary outcomes of interest are measures of *retention*, *compliance*, and *usability*.

- *Retention* will be defined as the amount of time participants remain active in the study. Specifically, the primary retention measure will be the number of days between the participant's first assigned study instrument and the date of the last assigned study instrument that they complete.
- *Compliance* will be defined as the number of instruments that the participant fully completes (i.e. responses for all required items) over the course of the study.
- *Usability* will be derived from a survey-based measure that assesses the perceived ease of use and pleasantness of the survey format (see separate attachment). The mean score across items of the survey measure will be used as the primary usability outcome measure of the overall usability of the survey format.

The exploratory outcome measures of interest are measures of *churn*, *engagement*, *activities*, and *routine*:

- *Churn* will be defined as missing more than 25% of assigned instruments within a study phase. Study phases will be defined at the 1 month, 3 month, and 6 month milestones.
- *Engagement* will be assessed based on participant behaviors while using the gamified mobile app (Arm A), and will include the number of clicks on the avatar, number of changes made to the avatar, number of gem store purchases, and the total amount of time spent on the app.
- *Activities* will be defined by classification of clusters of spatiotemporal geolocation data (Arm A).
- *Routine* will be defined by a directed graph model of the *activities*; characteristics will be explored using graph theoretic measures (Arm A).

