**Aim 1: Test whether electronic administration influences participant retention and compliance**

Hypothesis: There will be a significant difference in retention and compliance between paper and electronic (web) administration of surveys. Retention will be measured by the number of days from the first assigned instrument to the date of the last fully completed instrument and compliance will be measured by the number of fully completed instruments. Electronic administration will improve retention and compliance, such that administration on paper will have lower retention and compliance compared to electronic administration on the non-gamified websites (Datacubed Health website and third-party website).

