Each participant will be informed immediately of their group assignment and compensation scheme. Participants who are assigned to the mobile app group will receive additional instructions on how to download and log into the app. Participants who are assigned to the Datacubed Health website group will receive an email with instructions and a link to log into the Datacubed Health web portal. Participants who are assigned to the third-party website (Qualtrics) will be informed that they should expect to receive an email with a custom link to complete surveys each week. The third-party website will not be provided with any participant information, including email addresses. Subjects will only be identified to the third-party website with unique, randomly generated alphanumeric IDs. A script hosted by Datacubed Health will link these IDs to participant email addresses, internally. A master list of alphanumeric subject IDs and participant email addresses will be visible only to study administrative staff at Datacubed Health. Participants who are assigned to the paper group will be informed that they should expect to start receiving their surveys by mail each week.

Participants in all groups will be assigned the same set of study instruments, in the same order. See separate attachments for a listing and full text of all planned survey instruments. Each instrument will take no more than 10 minutes to complete (including embedded instructions), but most will be substantially shorter (2-3 minutes).

Participants in the gamified mobile app condition must log into the mobile app and will see a rich user interface - this includes a customizable avatar, progress-tracking maps that are gradually revealed as study activities are completed, points earned by completing study activities that can be redeemed for virtual avatar accessories (e.g. a hat or sunglasses), and other appealingly designed features (e.g. animated confetti displayed when study activities are completed). Participants in the non-gamified web conditions (Datacubed Health and third-party) must log into the respective web platform and will simply see a scrollable list of available study activities. Participants in the paper condition will be mailed paper surveys, which they must return to the study team through mail using pre-addressed and stamped envelopes. Screenshots illustrating examples of each study condition are provided as a separate attachment.

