Certain demographic data, such as age (month and year of birth only; all subjects are under 90), gender, sex, ethnicity, education level, employment status, annual income level, and type of smartphone, will be collected from all participants. These data will be analyzed to see if they are associated with any differences in retention, compliance, and engagement. For security, these data will be encrypted and stored in separate files, which can only be referenced through the anonymous subject ID that is assigned to each participant for the study.

Survey data, including survey responses, number of surveys completed, and dates of survey completed will be collected for all participants. These data will be used to evaluate the study endpoints of participant retention, compliance, and usability.

In addition to the aforementioned data types, for the group assigned to the gamified mobile app, several types of data provided by the phone operating system will be collected:

- **Passive data:** These types of data will be collected even when the participant is not actively using the app. Specifically, the app will record information about the participant's

phone battery percentage, geolocation, number of steps taken, apps installed on the phone, and phone screen on/off times. Participants will be fully informed during the consent process that the app will collect such data. They will be able to disable collection of location and step count data at any time by restricting the app permissions via the phone operating system; Android phone owners will also be able to restrict permissions for data collection on screen time.

- Geolocation is the collection of precise geographical location (latitude and longitude) of a device through a mixture of GPS and WiFi signals. This technology is used by many other apps that provide services based on a user's location, such as navigation, rideshare, banking, dating, and fitness apps. When location permissions are allowed, location data is sent to the app every few minutes. In this study, geolocation data will only be used to develop a data-driven model of participants' daily routines. This model will then be compared with self-reported measures of daily activity to see if geolocation data can serve as a measure of activity and routine. Datacubed Health will not share geolocation data with any other external parties and will destroy this data at the end of the study.

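### Retention ends at an unspecified date and has no value for participants who complete nothing; under the natural reading the paper arm gains mail-transit days

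*Protocol*

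**What the plan says.** Retention is a primary outcome (Protocol, Section 8) and is tested in Aims 1, 2 and 4. Section 8 gives the concept as "the amount of time participants remain active in the study" and the measure as the count of days between the "first assigned study instrument and the date of the last assigned study instrument that they complete". Aim 1 in Section 2 has: "Retention will be measured by the number of days from the first assigned instrument to the date of the last fully completed instrument". Compliance, the count of fully completed instruments, is a separate primary outcome.

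On dates, Section 9 (Arms A-D) says: "Survey data, including survey responses, number of surveys completed, and dates of survey completed will be collected for all participants". The same section says that paper participants are mailed their surveys, "which they must return to the study team through mail using pre-addressed and stamped envelopes", while web participants "will simply see a scrollable list of available study activities". No rule for dating a paper form and no completion window is stated.

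Section 21 foresees participants who complete no survey and earn $0. Section 13 treats people who silently stop returning surveys as non-compliant, not as withdrawn. Section 11 plans a one-way ANOVA with Dunnett's test for Aims 1 and 2, and allows the Kruskal-Wallis test if ANOVA assumptions are significantly violated.

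**The concern.** The two definitions share one gap: the date that stops the clock could be the day the instrument was assigned, the day it was filled in, or the day it reached the study team. In the web arms these can nearly coincide. In the paper arm they are separated by mail. If the clock starts when the form is sent and stops at completion or receipt, Arm C is measured on a longer clock than Arms B and D for the same behaviour. That works against the Aim 1 hypothesis that paper retains worse.

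The second gap does not depend on the reading. A participant with no completed instrument has no closing date and therefore no retention value. The protocol expects such people and keeps them in the study, so someone must decide whether they score 0 or leave the analysis. If that is decided after the data are seen, it is a data-dependent choice on a primary outcome.

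**Working it through.** **Scale.** Section 21 gives up to $130 at $5 per week: 130 / 5 = 26 weekly instruments, which reproduces its 26 weeks. With instrument k assigned on day 7(k − 1), the last is assigned on day 7 × 25 = 175. The protocol gives no SD, effect size or power for retention, so there is no sample-size figure to reproduce.

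**One participant, three readings.** Someone who completes all 26 on the day they are available scores 175 on the web under every reading. On paper, with 3 days each way, the score is 175 by assignment, 175 + 3 = 178 by completion and 175 + 6 = 181 by receipt. With 5 days each way, receipt gives 185. The readings can also diverge widely within an arm: completing only instrument 1, at the very end, scores 0 by assignment but about 26 × 7 = 182 by completion.

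**Identical behaviour in two arms.** Simulation of one paper and one web arm, 100 each (Section 9), two-sided 0.05, 2,000 runs. Assumptions not in the documents: 85% weekly response while active; 50%, 70% or 90% active to week 26; response delay 0 to 3 days; 5% never start, scored 0. The range is over the three activity levels; the SD was 47 to 63 days.

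| Dating, transit out + back | Paper minus web (days) | False rejection, t-test | False rejection, Kruskal-Wallis |
|---|---|---|---|
| Assignment | −0.1 to 0.3 | 0.048–0.051 | 0.050–0.055 |
| Completion, 3 out | 2.9 to 3.0 | 0.059–0.071 | 0.597–1.000 |
| Receipt, 3 + 3 | 5.6 to 5.8 | 0.098–0.136 | 0.748–1.000 |
| Receipt, 5 + 5 | 9.4 to 9.9 | 0.198–0.308 | 0.910–1.000 |

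A separate simulation with 3 days outbound gave 0.05–0.12 by t-test and 0.41–1.00 by Kruskal-Wallis.

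Hand check of the t-test at 70% active, 5 + 5: SE = 58 × √(2/100) = 8.20; 9.4 / 8.20 = 1.15; P(Z > 1.96 − 1.15) ≈ 0.21, against 0.212 simulated.

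The rank test suffers more because most participants sit near the ceiling, where a few days are enough to order one arm above the other. The same ceiling makes the data non-normal, so the fallback is a likely choice. Longer and more variable response delays than the assumed 0 to 3 days would dilute the effect.

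**Never-completers.** Dated by assignment, so no transit effect; 70% active to week 26; 5% never start on web.

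| Never start on paper | Rule | Paper minus web (days) | Rejection, t-test | Rejection, Kruskal-Wallis |
|---|---|---|---|---|
| 15% | scored 0 | −14.9 | 0.371 | 0.264 |
| 15% | excluded | 0.0 | 0.055 | 0.043 |
| 25% | scored 0 | −29.8 | 0.864 | 0.742 |
| 25% | excluded | −0.2 | 0.051 | 0.057 |

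The differences equal the excess share of never-starters times a mean of about 149 days among starters: 0.10 × 149 = 14.9 and 0.20 × 149 = 29.8. As no transit enters, the same arithmetic applies to Aim 2 with the app arm in place of paper.

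**The case against.** The strongest reply is that the protocol does not commit to the biased reading. Dated by assignment, transit contributes nothing, and a paper clock that starts at mailing is nowhere stated. That stands: a reader might infer that Aim 1 is biased towards paper as written, but the text supports only that it is ambiguous and that the natural reading has this consequence. It is also fair that dating and zero-completion rules are often left to a statistical analysis plan, which is not at hand. Against that, the protocol itself fixes the definition of a primary outcome, twice, and as fixed it cannot score every participant.

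Four stronger readings are tempting and should not be drawn.

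- *One late survey makes the measure worthless.* Completing only instrument 26 does score 175, while completing instruments 1 to 13 scores 7 × 12 = 84. But time to last activity is a legitimate retention concept, and compliance, also primary, records 1 against 13.
- *Delay costs nothing in the lump-sum cohort.* Both cohorts earn $5 per completed survey, so doing 1 of 26 forfeits 25 × $5 = $125 in either. At most, late completion of old surveys is cheaper under a lump sum, if old surveys stay open. No window is stated, but counting missed instruments within study phases (Section 8) and paying per week of completed surveys (Sections 9 and 21) hint at one.
- *Never-completers will be dropped, mostly from the app arm.* No passage says that they are excluded or where they would cluster.
- *Aim 1 loses a definite amount of power.* With no SD or effect size in the protocol, such a figure would be invented.

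**Conclusion.** The point holds in two parts.

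First, the closing date of a primary outcome is ambiguous. Under completion or receipt dating, with the paper clock starting at mailing, Arm C gains about 3 to 10 days of a 175-day scale for identical behaviour, given an assumed 3 to 5 days of transit each way. This is modest for the comparison of means (false rejection about 0.05 to 0.3) and serious for the Kruskal-Wallis fallback (about 0.4 to 1.0). These rates come from a two-arm comparison, not the planned three-group ANOVA with Dunnett's test, so they show the mechanism and its order of size rather than exact error rates.

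Second, retention is undefined for anyone who completes nothing, under every reading. The choice between 0 and exclusion has little effect on the arm difference when never-start rates are equal. If they differ by 10 to 20 percentage points, it moves that difference by about 15 to 30 days, enough to change the Aim 1 or Aim 2 conclusion.

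Transit times, response patterns and never-start rates are assumptions, and the SDs follow from them. The two gaps in the wording are not.

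**What to change.** Use one definition in Section 2 (Aim 1) and Section 8, for all arms:

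- Retention is the scheduled assignment date of the last fully completed instrument minus the assignment date of the first instrument. In the simulation this returns false rejection to about 0.05 for both tests.
- An instrument counts only if submitted, or postmarked for paper, within one common window, so that clearing a backlog at the end does not count. The window should be wide enough to absorb outbound mail, or the transit difference re-enters through it.
- Anyone assigned who completes no instrument has retention 0. Compliance is already 0 by definition and needs no rule.
- Everyone assigned is analysed. The calendar-date version is kept as a sensitivity analysis.

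The cost is wording and programming, plus noting the postmark on returned paper forms. Assignment dates follow from the schedule. The small downside is weekly instead of daily resolution. The change does not alter the score of someone who completes only the last survey on time: that is still full retention, so retention should be reported and read alongside compliance.
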